# Study protocol for a stepped-wedge, randomized controlled trial to evaluate implementation of a suicide risk identification model among behavioral health patients in three large health systems

**DOI:** 10.1186/s12888-025-06760-0

**Published:** 2025-04-08

**Keywords:** Suicide risk identification, Suicide prevention, Implementation

## Abstract

**Background:**

Age-adjusted suicide rates have increased in the U.S. over the past 25 years. Algorithm-based methods for identifying individuals at risk for suicide based on electronic health record and claims data have been validated but few studies have evaluated implementation or effects on population-level suicide attempt rates.

**Methods:**

This hybrid type I effectiveness-implementation pragmatic clinical trial will test a suicide risk identification model in behavioral health clinics at three large health systems. Local decision-makers will determine implementation specifics at each site. Clinics within each health system will be randomized to determine order of implementation. A stepped-wedge design using repeated measures pre/post-implementation maximizes statistical efficiency and power with fewer participants compared to a parallel design while allowing all clinics to participate. A pre-implementation period will serve as the baseline. The primary outcome will be the rate of suicide attempt per 1000 visits at 90- and 180-days following a behavioral health visit in which an individual was identified by the suicide risk model compared with the baseline period (no use of suicide risk model). Secondary outcomes include identification of suicide risk and recognition of individuals at risk for suicide (e.g., completed risk assessment), both compared to the baseline period. Generalized linear mixed models will be used to account for clustering within clinics and repeated measures over time, adjusting for relevant covariates to estimate the effect of the suicide risk model on outcomes. Implementation outcomes, including system-level determinants and clinician acceptance and use of the suicide risk model, will also be measured.

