**Fig. 1 Fig1:**
[figure not shown]
Stepped wedge design and study timeline

All individuals being seen in behavioral health care in one of the participating clinics are eligible for the trial, there are no exclusion criteria. Individuals included in the trial are not prohibited from seeking any care or services. Enrollment is anticipated to end July 2025.

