### Study measures and effectiveness outcomes

The primary outcome measure is fatal or non-fatal suicide attempt (binary yes/no) within 90 or 180 days of a behavioral health visit as measured using diagnosis codes for intentional self-harm (International Statistical Classification of Diseases and Related Health Problems, Tenth Revision [ICD-10] codes X60-X84; Y87.0). Suicide deaths will be ascertained from government mortality records. The denominator will be the total number of visits to behavioral health clinics and the numerator will be reported as the number of suicide attempts per 1000 visits. In addition to the primary outcome, we will examine proximal outcomes and crisis utilization measures. Proximal outcomes include measures of engagement with services documented in the EHR within the observation period. These are defined as: evidence-based suicide prevention interventions (safety planning, lethal means counseling, or caring contacts) on or after the risk identification (index) encounter, an outpatient encounter (includes telephone, virtual, and office visits) by a behavioral health clinician or psychiatrist subsequent to the index encounter, any contact with behavioral health within seven or 14 days of the index visit (includes phone calls, letters, patient portal messages, or other caring contacts in addition to encounters described above), frequency of contacts, latency to next encounter after index, and persistence in psychotherapy defined as no gap in psychotherapy visits > 90 days during the observation period. Crisis utilization measures include any encounters in the emergency department or inpatient stays subsequent to the index encounter within 90 days and 180 days.

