Secondary outcomes include suicide risk identification and recognition. Identification will be measured by the number and proportion of patients estimated to be at elevated risk by PHQ9 item 9, the risk model, or both, stratified by race/ethnicity. This will be assessed at each visit, as multiple visits may occur for the same individual. However, when calculating identification and recognition, we will aggregate visits at the individual level—categorizing outcomes as yes/no for binary measures and recording the number of identifications and recognitions as count outcomes. Aggregated assessment results will be generated at 90 and 180 days. Therefore, the denominator is the number of unique patients with an encounter in the study period. In the intervention clinics we will also measure the number of patients flagged by the risk model who, at the index encounter, did not complete the PHQ9 or denied item 9. Those identified by the risk flag but not through traditional PHQ-9 will represent the gain from using a model-based identification approach; in the usual care model these patients would not be identified as having elevated estimated increased risk. Suicide risk recognition will be measured by the number and proportion of patients who complete a risk assessment (C-SSRS), stratified by race/ethnicity, where the denominator is the number of unique patients with an encounter in the study period. We will also measure the proportion who completed a C-SSRS but did not have an elevated PHQ9 item 9 score but were estimated to be at elevated risk by the suicide risk model (for comparison, this will also be measured among usual care control participants as some patients will receive risk assessments independent of prompting by PHQ9 item 9 score).

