### Sample size and power analysis

We anticipate including > 50 clinics and approximately 395,000 unique behavioral health patients across three sites over a 2.5-year period, leading to over 1 million patient visits. We project that approximately 4–5% of patients will be identified as high risk and thus eligible for the intervention. Utilizing a stepped-wedge cluster randomized controlled trial design, with > 50 clinics randomly assigned across three waves, we will assess the primary outcome, suicide attempts, at 90- and 180-days post-intervention. Given an anticipated suicide attempt rate of 0.6% (*n* = 2,370) within 90 days of a visit, a 0.01 intraclass correlation coefficient within waves, we expect to achieve more than 80% power (2-sided *p* <.05) to detect an effect size corresponding to a 1.5% absolute difference in suicide attempt rates [47–49].

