These models will also be used to test mediators/mechanisms, given that we hypothesize that identification alone will not reduce suicide outcomes but rather increase the number of people receiving suicide intervention, which could lead to improvement (i.e., decrease) in suicide outcomes. Mechanisms include interaction with the alert and initiation of assessment, which starts the outpatient care pathway. We will also stratify analyses by health system site, and test for mental health diagnoses and prior suicide attempts as moderators. Importantly, we will exclude ‘training’ months for each phase of clinic implementation from the main analyses, since clinicians and patients may be partially exposed as the models are implemented and clinicians trained. In a secondary set of analyses, we will explore potential heterogeneity in treatment effects between clinics. Here we will conduct additional analyses to test within cluster comparisons of exposed and unexposed periods.

To examine the effectiveness of a suicide risk model on health service engagement and suicide attempt outcomes, we will start with similar descriptive and GLMMs analyses proposed previously for identification and recognition. The analyses here will focus on each unique health service engagement (supportive and crisis encounters separately) and suicide attempt outcomes, stratified by exposed (intervention) versus unexposed (control) groups. Suicide attempts will be captured by health system records using ICD-10 diagnosis codes occurring within the same 90-day and 180-day time periods. We will also use a Kaplan-Meier method and Cox-proportional hazards models to examine time-to-event for health service engagement and suicide attempts, with statistical adjustment for clinical and demographic factors. Individuals will be censored at the time of death or at 180 days past the index visit. We will again add terms for calendar month as well as site to account for variation by season and health system.

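### The primary outcome is stated on model-flagged visits in the abstract and on all behavioral health visits in the Methods, and the abstract's contrast, applied literally, is biased by selection

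*Protocol article*

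**What the plan says.** Two places in the protocol article define the primary outcome.

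- **Abstract, Methods.** The outcome is the attempt rate per 1000 visits at 90 and 180 days "following a behavioral health visit in which an individual was identified by the suicide risk model compared with the baseline period". The abstract describes that baseline as a time when the model is not in use.
- **Study measures and effectiveness outcomes.** The outcome is a fatal or non-fatal attempt "within 90 or 180 days of a behavioral health visit as measured using diagnosis codes for intentional self-harm". No flag is required, and "The denominator will be the total number of visits to behavioral health clinics".

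Three other places bear on which is meant.

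- **Clinic randomization and eligibility.** "All individuals being seen in behavioral health care in one of the participating clinics are eligible for the trial", with no exclusions.
- **Analysis plan for effectiveness outcomes.** The models address "suicide attempt outcomes, stratified by exposed (intervention) versus unexposed (control) groups". They are not restricted to flagged visits.
- **Sample size and power analysis.** The projection is "approximately 395,000 unique behavioral health patients across three sites over a 2.5-year period", a 0.6% attempt rate within 90 days of a visit (2,370 events), and more than 80% power for a 1.5% absolute difference. The same paragraph expects the model to flag some 4–5% of patients and treats only those as candidates for the intervention.

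**The concern.** The two definitions are different estimands. One is the attempt rate after visits at which the model raised a flag; the other is the attempt rate after every visit in the clinic. By the article's own projection, the flagged patients are about one in twenty to one in twenty-five of the population.

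The abstract's version has a further problem. Its intervention side is selected by the risk model, while its baseline side is described only as a period without the model. If nobody applies the same selection to baseline visits, the groups differ in risk by construction, and the comparison will point towards harm whether or not the alert does anything.

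Because this is the primary outcome, two published definitions also leave room to settle the denominator after the data are seen.

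**Working it through.** **1. Which denominator does the power section use?**
Inputs: 395,000 patients and a 0.6% rate (Sample size and power analysis).
0.006 × 395,000 = 2,370, exactly the stated count. The events are therefore counted over all patients, in line with the Methods definition and not the abstract. (The unit is patients, whereas both outcome definitions are per 1000 visits.)

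**2. How large is the flagged group?**
0.04 × 395,000 = 15,800 and 0.05 × 395,000 = 19,750 patients. The two candidate populations differ 20- to 25-fold.

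**3. Does the stated effect fit the stated rate?**
0.6% − 1.5 points = −0.9%. No reduction of that size exists on the all-patient rate. It is arithmetically possible only in a group whose rate exceeds 1.5%. So the paragraph takes its event count from all patients and an effect size that could be a reduction only in a higher-risk group.

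**4. What would the abstract's contrast show with no true effect?**
Rate ratio = (rate after flagged visits) ÷ (rate after all baseline visits). The denominator is taken as 0.6%. The numerator is not in the article, so it is assumed:

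| Assumed flagged 90-day rate | Ratio to 0.6% | Share of all attempts, at 4.5% flagged |
|---|---|---|
| 2% | 3.3 | 0.045 × 0.02 / 0.006 = 15% |
| 4% | 6.7 | 30% |
| 6% | 10.0 | 45% |

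As a cross-check, take the C-statistics of 0.83 to 0.86 quoted in the Background, assume a binormal ROC curve, and flag the top 4–5%. The flagged rate is then about 4.5–6.0%, a ratio of 7.5 to 10. If flagged patients are instead assumed to carry 20–60% of all attempts, the ratio (share of attempts ÷ share flagged) runs from 0.20/0.05 = 4 to 0.60/0.04 = 15. The size depends on the assumption. The direction requires only that the model discriminates better than chance.

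**5. Does any section supply a matching flagged comparator?**
Study measures and effectiveness outcomes says of one secondary recognition measure, which involves model-estimated risk, that "this will also be measured among usual care control participants". That suggests control visits might be scored, but the remark concerns C-SSRS completion and does not mention the primary outcome. Nothing in the article says that control-period visits will be scored to form a comparator for suicide attempts.

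**The case against.** The strongest reply is that the Methods already settle the matter. The formal definition names its denominator, eligibility is universal, the analysis contrasts exposed with unexposed without a flag condition, and 2,370 is an all-patient count. On this view the flagged-visit wording is one compressed sentence in an abstract. Most of that stands: all visits, exposed versus unexposed, looks like the working definition. It does not remove the contradiction, because the abstract states a different primary outcome outright and the power paragraph leans both ways.

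A reader might infer three stronger conclusions that the documents do not support.

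- *That the trial plans a biased comparison.* No analysis section sets flagged intervention visits against unselected baseline visits. Saying that the model is not used at baseline also does not rule out scoring those visits later. The bias arises only if the abstract is applied as written.
- *That the trial has no single primary question.* The weight of the Methods is on one side.
- *That the all-visit definition is itself an error because it dilutes the effect.* Dilution is real: an assumed 20% reduction among the flagged becomes 3%, 6% or 9% overall at flagged rates of 2%, 4% or 6% (0.20 × the shares in the table). But an all-visit contrast is a legitimate population-level estimand for a clinic-randomized trial, and it avoids conditioning on a score measured after crossover. Restricting to flagged visits would not cure low power either. Under the same assumptions, a Hussey–Hughes calculation (53 clinics, three waves, four periods, clinic-level ICC 0.01, patients as the unit) gives about 7–21% power in all 395,000 patients and 19–48% in 17,775 flagged patients. These figures depend wholly on the assumed inputs and bear on sample size, not on the contradiction.

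**Conclusion.** The inconsistency is real and concerns the primary outcome. The abstract and the Methods name different sets of visits. The surrounding text favors all visits but is not clean, because the power paragraph combines an all-patient event count with an effect that cannot be a reduction from that rate.

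That the definitions conflict, and that 1.5 points exceeds 0.6%, follows from the text alone. The 3- to 10-fold spurious excess is illustrative: it assumes a 2–6% rate after flagged visits, 0.6% after baseline visits, no intervention effect, and literal use of the abstract's contrast. The documents do not show that this contrast will be run. They do publish it as the primary outcome, and it should not stand.

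**What to change.** Name one primary analysis set, define it identically in control and intervention periods, and use the same wording in the abstract, the study measures section and the power section.

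- **Simplest repair.** Correct the abstract to the Methods definition (all behavioral health visits, exposed versus unexposed periods), and restate the power for that denominator with an effect that is possible from a 0.6% rate.
- **Supportive analysis.** A like-for-like comparison of visits at or above the alert threshold can be prespecified, with control-period visits scored retrospectively on stored EHR data.
- **If the sponsor intends flagged visits as primary.** The same threshold must be applied to control-period visits, and the study measures and power sections rewritten to match.

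The simplest repair costs wording and a recalculated power statement. The other two add scoring of stored data and carry a limitation: scores after crossover may shift because care has changed. A sensitivity analysis on each patient's first post-crossover visit would help to gauge that.

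### The abstract defines the primary outcome on model-flagged visits and the Methods define it on all behavioral health visits; these are different estimands, and the flagged version has no stated baseline comparator

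*Protocol article*

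**What the plan says.** The protocol article defines the primary outcome twice.

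- **Abstract, Methods.** The rate is per 1000 visits at 90 and 180 days "following a behavioral health visit in which an individual was identified by the suicide risk model compared with the baseline period", and the baseline is described as "no use of suicide risk model".
- **Study measures and effectiveness outcomes.** The outcome is a fatal or non-fatal attempt "within 90 or 180 days of a behavioral health visit as measured using diagnosis codes for intentional self-harm". There is no flag condition. "The denominator will be the total number of visits to behavioral health clinics".

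Three other sections bear on which population is meant.

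- **Clinic randomization and eligibility:** "All individuals being seen in behavioral health care in one of the participating clinics are eligible for the trial". There are no exclusion criteria.
- **Sample size and power analysis:** "approximately 4–5% of patients will be identified as high risk and thus eligible for the intervention". The same paragraph counts events over all 395,000 patients, using an "anticipated suicide attempt rate of 0.6"%, and targets a 1.5% absolute difference.
- **Analysis plan for effectiveness outcomes:** attempts are compared between exposed and unexposed groups. For the Kaplan-Meier and Cox analyses, "Individuals will be censored at the time of death or at 180 days past the index visit". The index visit for attempts is not defined separately. In the section on study measures, the index encounter of the proximal outcomes is the one at which risk is identified.

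**The concern.** The first definition covers the few percent of visits with the highest predicted risk; the second covers every visit. One primary endpoint cannot rest on both.

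Two things are at stake. First, the effect being estimated differs even when both periods are handled alike. An effect that works through flagged visits is seen undiluted in one population and diluted by unflagged visits in the other. Second, the flagged version is open to a selection artefact. The model is not in use at baseline, and no section says which baseline visits would be compared. If they were left unscored, a high-risk subset would be set against a mixed group, and the sign of the result could reflect who was selected and not what the intervention did.

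**Working it through.** **The plan's own figure.** 395,000 × 0.006 = 2,370, which matches the event count in the power paragraph. That count is over all patients.

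**Does the power paragraph identify the population?** A 1.5-point reduction is impossible from 0.6% (0.6 − 1.5 < 0), but possible from the higher rate of a flagged group. I also computed Hussey-Hughes power for a 1.5-point difference, assuming 51 or 53 clinics, three waves, four periods and an ICC of 0.01 taken at clinic level.
- All 395,000 patients, 0.6% versus 2.1%: about 100%.
- Only the 4–5% flagged, with base rates of 4.6–6.2%: about 65–87%.

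The event count points to all patients and the effect size points to a flagged group. The paragraph does not decide the matter.

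**Inputs for the size of the discrepancy**
- Overall 90-day attempt rate π = 0.006 (Sample size and power analysis).
- Share flagged q = 0.04 or 0.05 (same section). It is given per patient; applying it to visits is my assumption.
- C-statistic 0.83–0.86 (Background). Carrying it over to these clinics is my assumption.
- Equal-variance binormal score: my assumption.

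**Formulas**
- Separation: d = √2 × Φ⁻¹(AUC), which is 1.349 for 0.83 and 1.528 for 0.86.
- Cut-off t solves π[1 − Φ(t − d)] + (1 − π)[1 − Φ(t)] = q.
- Sensitivity: s = 1 − Φ(t − d).
- Rate among flagged visits: π × s / q. Ratio to the all-visit rate: s / q.
- Rate ratio over all visits when attempts are halved among flagged visits only: 1 − 0.5 × s.

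| AUC | q | s | Flagged rate per 1000 | Null ratio, flagged vs all baseline visits | Same ratio after a true halving | All-visit ratio after a true halving |
|---|---|---|---|---|---|---|
| 0.83 | 4% | 0.336 | 50 | 8.4 | 4.2 | 0.83 |
| 0.83 | 5% | 0.376 | 45 | 7.5 | 3.8 | 0.81 |
| 0.86 | 4% | 0.402 | 60 | 10.0 | 5.0 | 0.80 |
| 0.86 | 5% | 0.444 | 53 | 8.9 | 4.4 | 0.78 |

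First row in full: 0.006 × 0.336 / 0.04 = 0.0504; 0.336 / 0.04 = 8.4; 1 − 0.5 × 0.336 = 0.83.

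**Like for like.** With the same visit set in both periods, the expected ratio under no effect is 1 for either definition. The halving then appears as 0.50 on flagged visits and as 0.78–0.83 on all visits.

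**Sensitivity to the ROC shape.** With unequal-variance binormal curves (slope 0.7 to 1.4) and a power-law ROC at the same C-statistics, the null ratio in the mismatched comparison runs from about 5 to about 15. The direction does not change.

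**The case against.** The Methods definition is explicit, sits in the section meant to define outcomes, and fits the open eligibility and the exposed-versus-unexposed comparison. On this view the abstract is one loosely worded sentence, and the definition that governs has no selection problem. Much of this stands. The Methods definition is unbiased on this point, and correcting the abstract may be all that is needed. It does not remove the conflict, because the power paragraph treats the flagged 4–5% as those eligible for the intervention and targets a difference that cannot be a reduction from the all-patient rate.

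A reader might infer more than the article supports, in three ways.

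- **That baseline has no matching visits.** This is not established. The abstract says only that the model is not in use then. The sites hold the EHR and claims data from which such models are derived, so earlier visits could be scored. The section on study measures also plans a secondary measure that involves model-estimated risk and says it will be measured in usual-care controls. No section extends this to the primary outcome.
- **That the trial will show a spurious rise of 7.5- to 10-fold.** That figure needs flagged intervention visits to be compared with all baseline visits, which no section plans. It also needs an assumed ROC shape and a per-patient share applied to visits.
- **That the censoring rule shows such a comparison is planned.** It does not. Identification can come from PHQ9 item 9, the model or both, so baseline index encounters can exist. They would be selected by a different route unless the same visit set is specified.

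**Conclusion.** The point holds as an internal contradiction about the primary endpoint. The abstract and the Methods give different populations, the power paragraph does not choose between them, and the flagged version lacks a stated baseline comparator.

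The firm consequence is a change of estimand: a halving confined to flagged visits reads as 0.50 or as about 0.78–0.83, depending on the definition. Those figures rest on the binormal assumption, 4–5% flagged at visit level and a C-statistic of 0.83–0.86. The apparent rise under no effect (about 7.5- to 10-fold, or 5- to 15-fold across ROC shapes) is a conditional risk. It arises only if the abstract's version is analysed with baseline visits left unscored. The conflict should be resolved before outcomes are analysed, because it decides what the primary result means.

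**What to change.** State one primary population in the abstract, the outcome definition, the power paragraph and the analysis plan. Either:

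1. correct the abstract to the Methods definition, with all behavioral health visits in both periods; or
2. if flagged visits are intended, score baseline visits with the same locked model and cut-off, compare flagged with flagged, and revise the denominator in the section on study measures to match.

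In either case, use the same visit set in both periods for the time-to-event analysis of attempts and define the index visit accordingly.

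Option 1 costs a text correction. Option 2 also needs retrospective scoring, from EHR and claims data that the article says the sites already hold. Under either option the power statement should be restated for the population chosen.
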